### Current study in the context of adversarial collaboration

It is important to contextualise the significance of this test of AI-C in the broader setting of the INTREPID adversarial collaboration; this is because scientific expectations for adversarial collaborations can differ from more common scientific projects. An adversarial collaboration is designed to be able to distinguish among theories, rather than just test theories on their own; this implies that experiments are designed for which each theory has a prediction. Where theories are relatively diverse in their explanatory target and theoretical construction, as may happen in early (pre-paradigmatic) phases of scientific development, a quite diverse set of experiments may be designed, each of which test one theory more directly than the other theories. Thus one theory may make a clear and confident prediction about a given experiment, while other theories that are not directly tested may need to appeal to certain auxiliary hypotheses to generate a prediction. This can have the effect that predictions from some theories though directional are held with low confidence (due to the added complexity from adding auxiliary hypotheses). Furthermore, the effort to define tests for which all theories can have predictions can lead to compromises where the tests are not in fact strongly pertinent to the subject matter of the theories but instead relate to a more peripheral prediction (for example, it may be about a particular neuronal response rather than a finding in paradigmatic consciousness science).

The challenges associated with testing diverse theories can be mitigated by adopting a multi-experiment strategy whereby different experiments are more weighted towards key theoretical predictions of one theory than another. Taken together, these experiments will yield a balanced set of results pertaining to a range of predictions that are capable of arbitrating amongst the theories of interest. The overall outcome of the adversarial collaboration will then depend on discussion of these results in light of each theory lead’s preregistered predictions and their associated confidences (which serve to weight the relevance of a given experimental outcome for one’s theory), and the significance of any confounds and unforeseen elements. In this context, some empirical results may only lead to modest distinction among theories, while others may lead to more stark distinctions; however, the implications for each theory will not be clear until the findings of each experiment have been combined. It is thus important not to pass judgement on the outcome of an adversarial collaboration until all experiments have been concluded and their results fully integrated under a single, overarching analysis scheme. In addition to conceptual interpretations, a Bayesian adversarial collaboration analysis scheme can formally describe these scenarios, and provide numerical outcomes for each theory’s predictions (including the prediction confidences) across all experiments, and compare even disparate theories with each other (as long as each theory has some prediction about all experiments) (see [34], which also surveys the philosophy of science of adversarial collaborations).

Notice further that, in the logic of an adversarial collaboration, the aim is to distinguish among the involved theories. The benefit of this is that researchers in the field are then provided with an evidence-base for deciding which of those theories to believe the most, or to invest their own research time and resources in. A potential limitation is that the results may not necessarily be substantially informative for theories outside of the adversarial collaboration; for example, it could be that a further theory exists that would make overlapping predictions with one of the theories in the adversarial collaboration. Hence, from the perspective of such a further theory, the findings may not be of interest, even if they do strongly distinguish between the involved theories.

In the current adversarial collaboration (TWCF ARC INTREPID), three main experiments have been designed, one of which, described in this study protocol, is pertinent to AI-C. All three theories have predictions (with varying confidences) about each experiment, and the aspiration is that the outcome will distinguish one theory from the other two. The complete set of prediction tables have been made available in the preregistration [35], and we set out the details of the prediction tables for our experiment, and provide a context for these in a schematic for the entire set of predictions in the section Operational Hypotheses below. We refer the reader to the preregistration and the Study Protocols for details concerning the other experiments.

## Materials and methods

### Aim

The aim of this study is to contrast passive and active conditions using peripheral targets in MIB. In the active condition—after the participant reports the initial disappearance (fading from awareness) of the stimulus—they will be cued to saccade to the previously observed location of the target. This saccade is considered as a manifestation of overt active inference. In the passive condition, following a reported disappearance, the sensory consequences of the saccade are ‘replayed’ by moving the stimulus array (which includes the grid), while central fixation is maintained. Passive replay will be based on eye movement trajectories recorded via eye tracking during the active condition, thereby ensuring that visual stimulation is identical across conditions. In each condition, participants will be instructed to indicate—via button press—when the target reappears in consciousness (see Fig 1).

**Fig 1 pone.0328836.g001:**
[figure not shown]
Schematic of trial timeline common to Experiment A and B. Thought bubble denotes perceptual (rather than physical) disappearance. The boxes after the forking cue arrows denote the distinction between the active (top) and passive (bottom) conditions. The circular arrow denotes motion of the gridded array (though its direction is randomly selected for each trial).

### Status and timeline

In the latter part of 2020, two Templeton World Charity Foundation workshops were hosted online by [name], resulting in (1) the formation of the TWCF INTREPID consortium, (2) the selection and fleshing out of experimental paradigms capable of arbitrating amongst hypotheses derived from IIT, NREP, and AI-C. From this, the consortium initially commenced piloting, testing the viability and feasibility of the experiments in mediating between theories. In mid-2021 the experiment team at Monash University convened a meeting agreeing with [name] from Friedrich Schiller University Jena to form the replication lab (impartial to the outcome) for the INTREPID consortium’s set of experiments testing the necessity of active inference for changes in conscious content. In late-2021 the Monash Lab ran piloting for proof-of-principle for the eye-tracking and behavioural components of the experiment. This design was then pre-registered on OSF (https://osf.io/35rhx) as part of the larger, multi-experiment structured adversarial collaboration (https://doi.org/10.54224/20646). Currently, piloting and paradigm development have been completed for both experiments and data collection is underway.

Based on this process, the experiments described herein form one of four protocols to be published, each describing experiments derived from predictions of the three theories being tested (AI-C, IIT, and NREP). Moving forward, consistent with the principles of a co-design, all amendments to the experiment protocol following this publication will be addressed by agreement between the teams at both Melbourne and Jena data collection sites, and the three INTREPID consortium theory leads ([name], [name], and [name]). Each amendment will be documented in experimental reports identifying the specific change and rationale. A set of general analysis principles will be agreed upon prior to the commencement of the study; however, analysis pipelines will be developed and run separately in each lab to mitigate the potential for idiosyncratic analysis decisions to bias results. This process will be overseen by the Data Analysis and Replication Committee (DARC) of the INTREPID Consortium.

### Participants, sample size, exclusion/inclusion criteria, and stopping rule

Experiments A and B will be conducted in parallel at the Monash Centre for Consciousness and Contemplative Studies, Monash University (Melbourne, Australia) and the Institute of Psychology, Friedrich Schiller University (Jena, Germany). Identical stimulus materials and programme scripts will be used to run the experiments on identical setups and under very similar circumstances.

Participants will be students and staff recruited through each institution’s internal recruitment system. The general public may also be recruited through email approaches based on flyer responses. Participants in Melbourne will be reimbursed for their time either with course credit or AUD$20-50; participants in Jena will receive a similar rate in Euros or partial course credits. Both research sites have received ethical approval from their respective University Human Research Ethics Committees (Monash Human Research Ethics Committee – Ethics Number: 29238; The Ethics Committee of the Friedrich Schiller University – Ethics Number: FSV 22/093.

Recent MIB work deploying eye-tracking and pupillometry in the MIB paradigm [36] aimed for a target sample size of 55 participants to give a statistical power of at least 80% with an effect size of η2p = .13.; we will adopt this sample size as a stopping point for data collection. Participants must have normal (or corrected-to-normal) vision and audition, and will be aged between 18 and 45 years. Additionally, participants must demonstrate computer literacy and be able to maintain constant fixation for at least 5 seconds in the pre-test period and follow the fixation-based gaze strategy. Respondents will be excluded from participation if they (1) report having previously suffered a stroke or other neurological condition; (2) are currently taking psychoactive medications; or (3) are currently undergoing mental health treatment.

In Experiment A, participants will be excluded if they fail to report disappearances in more than 50% of trials or if they fail to generate a reappearance response in more than 25% of trials where they reported a disappearance. In Experiment B, participants will be excluded if they fail to reach the masking boundary at which there is stimulus reappearance <50% of the time, or in other words, if they fail to reach a threshold of stimulus awareness. Here ‘masking boundary’ describes a virtual circle, centred on the stimulus. If participants’ gaze enters this region, the stimulus will physically disappear. The same 50% rejection criteria will apply for reported disappearance and similarly participants who fail to complete > 25% of trials (including fixation, pre-cue period; post-cue period) for any reason will be excluded from data analysis. Furthermore, participants who do not meet the behavioural, eye tracking (e.g., microsaccade, eye-blink, and gaze location) exclusion criteria listed in the Data pre-processing section (below) will also be excluded from further analysis. Participant data collection will be considered complete when the total number of participants who surpassed these rejection criteria meets the stopping point defined above.

### Experiment A: Time to reappearance following motion-induced blindness

**Design, stimuli, and procedure.** This experiment deploys a within-subjects design to contrast differences in the time to reappearance of stimuli rendered subjectively invisible by MIB. The MIB task will be performed in conjunction with eye tracking in order to produce both active looking blocks and passive viewing blocks (where the active gaze is precisely replayed).

We will use the Racially Diverse affective expression (RADIATE) face stimulus set [37]. We use only neutral faces for our stimulus set, removing any stimuli with accuracy ratings for neutral emotional state below 80%. This leaves 108 stimulus images of distinct identities (and one used solely for instructional purposes). On each trial, the stimuli will be pseudo-randomly sampled with a constraint that no greater than two consecutive repetitions of a specific identity will be shown to participants. Each target stimulus will be converted to greyscale, scaled to 200x200 pixels, and luminance-matched using the SHINE toolbox [38]. All images will be enclosed in an elliptical mask centred on the face shape. In order to correct the luminance difference created by the mask the luminance of each stimulus image will be scaled to match an RGB value of 100 (+/- 0.1%); the background colour of the display will also be matched to this value.

Target stimuli will be presented at a randomly-selected polar angle (1–360 degrees) 9 degrees of visual angle from central fixation. In each trial, a blue central fixation dot will be present behind the stimulus and a cross pattern filling the entire screen will rotate at 2.7s/cycle, in line with previous work [39]. As the target in this design will either (in the passive case) remain stationary after being moved into central fixation or (in the active case) be foveated by the participant, it will ultimately fill the centre of the visual field in both conditions. This means that central attentional resources will eventually be allocated to it, and it will become visible even in the passive condition. This is consistent with active inference, since attention is a (covert) form of action. However, the thrust of this experiment lies in the role of overt action (eye movement), recognizing that covert attentional resources are also deployed in the passive condition at some point in the task.

Experiment A sessions will be separated into three sections:

*Training*. A crucial consideration—in both the analysis of eye tracking data and the use of eye tracking data to construct a retinal matched replay—is that epochs are not disrupted by additional saccadic eye-movements. Therefore in both experiments we will employ a training procedure similar to that reported in a study using fixation-event epoching by Kaunitz and colleagues [40]. Following standard calibration and validation procedures, participants will be taught to maintain their gaze on a central fixation dot, followed by a randomly positioned peripheral target (9 degrees visual angle). Initially, participants will only have to fixate on each target for 1 second, but after each trial the goal will be increased (+1 second) based on successful fixation, for a maximum of 5 seconds. As in previous work, this procedure should help participants to learn to pace their saccade and fixation rate so that they take time before changing their gaze. In this training phase participants will also be shown a warning if they fail to maintain their fixations for the target length. Participants will be given a maximum of 20 trials of 20 seconds (~6.6 minutes max total) to achieve this training standard. If the participant is unable to reach the 5 second maximum before the end of the training phase they will not progress to the next phase of the experiment. The last part of the training will use a two trial (20 seconds each; 40 seconds total) demonstration of the phenomena of perceptual disappearance using a physically removed stimulus, in order to teach the participant to differentiate between potential transient disappearances and full perceptual disappearance (occurring around 5–15 second from the start of exposure). Accounting for instruction time, this section takes a maximum of 10 minutes.

*Practice Experiment.* Following training, participants will be told how to complete active and passive trials before the main experiment begins. To ensure that participants fully understand the task, they will first perform a practice version of the experiment. This will be a short version of the main experiment that will allow participants to be walked through the task, under the supervision of the experimenter. The participant will complete six active and six passive trials, this practice will be repeated if the participant fails to successfully complete more than half the practice trials. If participants do not complete at least six trials (even including repeats) they will not progress to the next stage of the experiment. Participants will receive a warning during this phase on any trial where: 1) The minimum eye-gaze time for fixating in the centre of the screen was not met; 2) they look at the target when not instructed to.

*Main experiment*. Following the successful completion of training and practice trials, participants will be reminded (via diagram) how to complete active and passive trials before the main experiment begins. Participants will be informed that a cue in the active trial will allow them to move their eyes to look at the location where the target was previously seen; in contrast, in the passive trials the cue is an instruction to maintain fixation. During each experimental trial, the participant will be initially required to perform an uninterrupted fixation on a central dot for at least 1.5 seconds before responses can be given. If the participant is unable to maintain eye gaze on the target for more than 1.5 seconds, they will not be able to complete the trial. If the participant looks at the peripheral target stimulus during this time period, the trial will automatically end (and will not be counted as a valid trial). The participant will then be asked to press a button when the peripheral target stimulus entirely disappears; following this response, after a short delay (randomly jittered between 500ms-1000ms) a cue will be given to signal the next phase by flashing a different colour of the central fixation. In the active trial block, after the cue, the participant will be asked to look to the target location. In the passive block, participants will be told to maintain central fixation while the entire visual display (including the rotating grid) moves in relation to the fixation cross to eventually position, in an exact replay, the stimulus as it was in a randomly selected trial from the active block. Crucially, in this version of the experiment participants will be asked to respond as soon as they become aware of the target, thereby generating an estimate of the time to reappearance.

Each trial will last a minimum of 4 seconds (1.5 seconds for fixation; 500 ms pre-cue delay; 2 seconds post-cue) and a maximum of 20 seconds, with a randomly selected inter-trial-interval (ITI) ranging 1.5–2 seconds (during which only a central fixation dot will be displayed). If the maximum trial time is reached—without all elements of the trial being completed—this trial will be removed from further analysis. Each condition will comprise 72 trials with a break every 24 trials (a trial block). In each block, two catch trials will be included; these will appear pseudo-randomly (excepting the first and last 3 trials) in each block and will involve the physical disappearance of the stimulus. Note that these catch trials will end as soon as the participant reports awareness of this disappearance. Blocks of active and passive trials will be interleaved such that 24 active trials will be followed by 24 replay trials until 144 (+12 catch trials) trials of each type have been shown. Each image will be shown a maximum of four times in the active trials. Accepted active replays will be carried across passive blocks but the angle of their movement trajectory towards the centre of the screen will be randomised. This will ensure that stimuli can be replayed in the passive block without leading to systematic confounds relating to a specific movement trajectory.

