### Current study

Here, we describe a set of two experiments that form one of four Study Protocols (to be published separately), each of which is developed based on predictions of one of three major consciousness theories being tested in this adversarial collaboration (AI-C, IIT, and NREP).

As described above, the test of AI-C’s hypothesis proceeds by curtailing active inference in one, ‘passive’ condition, and contrasting that with an ‘active’ condition in which active inference leads to the selection of a policy of action with high expected information gain, with the prediction being that the active condition facilitates conscious awareness of the target. We will pursue this idea in a motion-induced blindness (MIB) paradigm, where a stationary peripheral target is rendered invisible due to the motion of a global pattern. We will contrast active sampling (via overt eye movement) with passive sampling (with eyes remaining at fixation) where, crucially, participants are exposed to identical visual input and retinal activation, and other task, attentional and expectation-related factors are kept constant. To assess the key prediction from AI-C that changes in conscious content will systematically occur earlier in the active condition, post hoc reports will assess whether the passively processed changes to sensory input are perceived later than the actively sampled changes.

In this study, we employ two experiments designed to assess these MIB active-passive differences (For more specific operationalised predictions relevant to the three theories considered in the adversarial collaboration (IIT, AI-C, NREP), see the section Operational Hypotheses below):

*Experiment A: Do changes in conscious experience occur earlier in the active than the passive condition?* This experiment will test whether the duration of MIB differs across the active and passive conditions. If there is no difference between conditions, or if MIB persists longer in the active condition, then that is strong evidence against AI-C. If MIB persists for longer in the passive condition, this would predominantly support AI-C.

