### Operational hypotheses

The hypotheses being tested by the experiments described in this Study Protocol are as follows:

Experiment A: changes in conscious experience manifest earlier in the active than the passive condition, as measured by behavioural responses;

Experiment B: backward masking can preclude changes in conscious experience in the passive condition but not (as much) in the active condition.

These hypotheses stem from the putative role of active inference to confirm the sensory input expected following action (as described in the Introduction). Active sampling should promote faster resolution of uncertainty, engendering earlier perceptual inference. These hypotheses can be expressed in terms of the following predictions about the patterns of data we expect to observe in each experiment:

1]*Subjective report of reappearance of peripheral stimuli will occur after a shorter delay following subjective disappearance in the active vs. the passive condition of Experiment A* (see Table 1).2]*The psychophysical reappearance threshold for the radius of the masking boundary (once eye gaze is inside this invisible circular boundary the stimulus is masked) will be higher ; i.e., a larger radius in the active vs. the passive condition of Experiment B* (see Table 2).

**Table 1 pone.0328836.t001:** Predictions about the effect of active (vs. passive) sampling on target time-to-reappearance in Experiment A.

Theory	Decrease	No change	Increase	Confidence
IIT	X	X		Low
NREP	X	X		Medium
AI	X			High

**Table 2 pone.0328836.t002:** Predictions about the effect of active (vs. passive) sampling on mask onset boundary distance in Experiment B.

Theory	Decrease	No change	Increase	Confidence
IIT		X	X	Low
NREP		X	X	Medium
AI			X	High

Each of the other theories considered in the adversarial collaboration, IIT and NREP, offer different predictions to these, which also differ in their degree of confidence:

IIT is consistent with both manipulations (active or passive target sampling) quickly breaking suppression, by changing visual cortex state. Motor involvement (active) may be enough to tip the balance towards breaking suppression more easily, for a small difference in time to reappearance and/or masking boundary. Thus, for Experiment A (see Table 1), IIT predicts either decrease or no change, with low confidence; for Experiment B (see Table 2), IIT predicts either increase or no change, with low confidence.

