### Planned analyses and expected outcomes

In order to capture the contribution of covariates within both experiments, 3A and 3B dependent variables will be analysed under a generalized linear modelling framework based on a pre-specified decision tree (see Fig 3). The choice of link-function will be informed by the distributional properties of the data and the evaluation of standard model diagnostics (e.g., Q-Q plot of residuals) and indices of marginal likelihood (e.g., AIC). Nested model comparison will be used to evaluate whether model fit is significantly improved by the inclusion of focal parameters. Random effects and additional covariates accounting for potential sources of noise (e.g., mean inter-beat interval, time-on-task) may be included if warranted by theoretical considerations and model comparisons (for a similar approach, see [44]). As part of this analysis we will quantify microsaccades frequency and latencies, as well as pupil area trajectory. These findings will be included in the results and, if we find that any of these data features, when considering the period immediately following the cue, differ significantly between conditions we will include these as covariates in the model.

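### Participants can know the condition when they report the disappearance that triggers the cue, so attention and expectation are not held constant, and the article states no check of pre-cue differences by condition

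*Protocol article*

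**What the plan says.** All references are to the protocol article.

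- **Order of conditions** (Experiment A, Main experiment): "Blocks of active and passive trials will be interleaved such that 24 active trials will be followed by 24 replay trials". Experiment B follows the same general procedure.
- **Instructions** (same section): participants learn beforehand what the cue means in each trial type: "Participants will be informed that a cue in the active trial will allow them to move their eyes". The passive instruction is tied to the block: "In the passive block, participants will be told to maintain central fixation".
- **Entry to the cue phase** (same section): "The participant will then be asked to press a button when the peripheral target stimulus entirely disappears", and then "after a short delay (randomly jittered between 500ms-1000ms) a cue will be given to signal the next phase".
- **Outcome of Experiment A** (Operational hypotheses): the prediction is that reappearance "will occur after a shorter delay following subjective disappearance in the active vs. the passive condition".
- **Claimed control** (Current study): retinal input is identical and "other task, attentional and expectation-related factors are kept constant".
- **Covariate trigger** (Planned analyses and expected outcomes): if microsaccade or pupil features, "when considering the period immediately following the cue, differ significantly between conditions we will include these as covariates in the model". Other covariates, with inter-beat interval and time-on-task as examples, are optional.

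**The concern.** The disappearance press is subjective. It decides whether and when a trial reaches the cue, and in Experiment A the predicted delay is counted from it. In an active block the participant can expect to look at the target's location next. In a passive block the participant can expect to keep fixating. That knowledge may change how much attention goes to the target before the cue, how strict the participant is about complete disappearance, and how deeply the target is suppressed when the cue comes.

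If one condition lets in more weakly suppressed trials, it will tend to show earlier reappearance in Experiment A and more frequent reappearance reports in Experiment B, with no contribution from the saccade. The bias could run either way and so imitate or hide the AI-C prediction. The claim of constancy in the Current study section is what allows an active-passive difference to be attributed to active sampling, so its accuracy matters. Counterbalancing the block order would not help, because the condition would still be known within each block.

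**Working it through.** **1. Is the condition knowable before the press?** Runs of 24 in fixed alternation, with instructions given by block, make it so after the start of a block at the latest. The press comes 500-1000 ms before the cue.

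**2. Does the replay equate the conditions at that moment?** No. The eye-movement replay section sets the replay window from the cue to the first fixation on the target. It matches input from the cue onward and cannot equate the state at the earlier press.

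**3. What do the stated safeguards do?**

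| Safeguard | Section | Effect on this issue |
|---|---|---|
| Two demonstration trials contrasting transient with full disappearance | Training | Trains the criterion; does not show it is equal across conditions |
| Reject any press under 3 s from trial start | Data collection procedures | Removes the earliest reports in both conditions |
| Reject reappearance under 250 ms after the cue | Data collection procedures | In Experiment A a target must stay unreported for at least 500 + 250 = 750 ms after the press; screens out some weakly suppressed trials |
| Two catch trials per block | Experiment A, Main experiment | Yields disappearance data in both conditions; no comparison by condition is stated |
| Exclusion on disappearance reports | Participants, sample size | At participant level, not by condition |
| Cardiac and pupil measures | Current study; Discussion | Proxies for arousal, not for a response criterion |
| Automatic microsaccade and pupil trigger | Planned analyses | Considers only the period after the cue |

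These reduce the problem. None tests whether the criterion differs by condition.

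**4. The plan's own sample-size figure.** Inputs from the sample-size section: n = 55, power at least 80%, η²p = .13. Assumed, because not stated: two-sided 5% test of a paired contrast.

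- f² = .13 / (1 - .13) = 0.149, so the standardised within-person difference is √0.149 = 0.387.
- Noncentrality = 55 × 0.149 = 8.22, with F(1, 54).
- Power = 80.4%, and 55 is the smallest n that reaches 80%. The stated figure is reproduced.

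**5. Illustration of sensitivity.** The same function is used with zero true effect and a bias of b SDs of the within-person difference, so noncentrality = 55 × b².

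| b (assumed) | Noncentrality | Rejection rate |
|---|---|---|
| 0 | 0 | 5% |
| 0.1 | 0.55 | 11% |
| 0.2 | 2.20 | 31% |
| 0.3 | 4.95 | 59% |
| 0.387 | 8.22 | 80% |

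**6. Can b be narrowed?** Write b = (extra share of weakly suppressed trials × time gap) / SD of the difference. All three are assumptions.

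- Low case: 2% × 100 ms = 2 ms; at SD 80 ms, b = 0.025 and the rejection rate is 5.4%.
- Middle case: 10% × 200 ms = 20 ms; at SD 80 ms, b = 0.25 and the rate is 45%.
- High case: 10% × 300 ms = 30 ms; at SD 40 ms, b = 0.75 and the rate is practically 100%.

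The range runs from almost nothing to near certainty. The arithmetic shows sensitivity to a small bias, not its likely size. It concerns a paired difference in time; nothing was computed for Experiment B, whose outcome is a boundary-radius threshold.

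**The case against.** Several counter-arguments have force.

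- **The covariate list is open.** Planned analyses gives only examples and points to a decision tree in Fig 3, which is not visible here. Eye data are recorded throughout, and the analysis epochs extend before the cue. A reader might infer that the plan cannot or will not adjust for any pre-cue difference; the document does not support that. What stands is narrower: the automatic trigger is stated, and it looks only after the cue.
- **Blocks are not said to be announced.** No sentence says so. That participants can know the condition is an inference from fixed alternation and block-level instruction, though a safe one.
- **Saccade preparation is part of the contrast.** The Introduction counts planning and covert attention as active inference and contrasts a policy of fixating with a policy of foveating, so some pre-cue difference belongs to the active condition as AI-C conceives it. This stands. It does not cover a shift in the disappearance criterion, and it sits badly with a claim that attention and expectation are constant.
- **Disappearance latency may itself respond to condition.** Forcing it into the primary model could remove part of the effect under test or introduce bias. This stands, and it limits latency to a sensitivity model.

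**Conclusion.** The concern holds in a limited form. The blocked design lets the condition be known before the report that admits the trial, so the statement that attentional and expectation-related factors are constant describes a property the design does not have. The existing safeguards lessen the risk without testing it.

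A reader might infer from the rejection rates above that the trial is likely to give a false positive. The documents do not support that: they give no size or direction for a criterion shift and no SD for the within-person difference. The 31% at 0.2 SD is an illustration resting on an assumed bias and an assumed two-sided 5% paired test, and it does not carry over to Experiment B. What is established is that a pre-cue difference could go unexamined and be attributed to the eye movement. It can be checked with data already being collected.

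**What to change.** Keep the blocks, since data collection is underway, and keep the primary model.

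1. Prespecify, for Experiments A and B, a comparison between active and passive trials of disappearance-report rate, disappearance latency (trial start to press) and catch-trial responses. Report it beside the main contrast.
2. Add a sensitivity model with trial-level disappearance latency as a covariate. State that latency may itself be affected by condition and captures the criterion only in part.
3. Amend the Current study section to say that retinal input is matched from the cue onward, that condition was predictable before the disappearance report, and that an active-passive difference accompanied by a pre-cue difference will not be attributed to the eye movement alone.

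The cost is a descriptive table and one extra model per experiment from existing timestamps, plus a narrower claim recorded through the plan's amendment route. No new data are needed. The remaining limit is that a criterion shift which leaves rate, latency and catch-trial responses unchanged would still go undetected.
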